## Abstract

**Background:**

Cocaine is the most frequently used stimulant worldwide, with increasing consumption rates in Europe. Cocaine use is associated with great harm to individuals and society. As of today, psychotherapeutic interventions for cocaine use disorder (CUD) demonstrate only modest effect sizes, and no pharmacotherapy has been approved due to gaps in understanding the disease. However, a novel pharmacotherapeutic target, i.e. glutamatergic neurotransmission, emerged from animal models of addiction. Specifically, after chronic cocaine administration, glutamate concentrations in the nucleus accumbens (NAcc) of rodents are reduced, while there is an overflow of glutamate during cue-induced cocaine-seeking. Recently, this glutamatergic imbalance has also been observed in humans with CUD. Additionally, promising findings with regard to novel psychotherapeutic approaches came from neurofeedback training (NFT) studies where participants use cognitive strategies to regulate their activity within a specific brain region based on “real-time” feedback about its activity as assessed by real-time functional magnetic resonance imaging (rt-fMRI). For example, participants with CUD successfully learned to regulate their brain activity in reward areas of the midbrain using reward imagery and to reconstitute reward sensitivity to non-drug related reinforcers like, e.g. social interactions, athletic or professional achievements. We therefore investigate the therapeutic potential and the underlying mechanisms of two interventions, a single dose of ketamine and a reward imagery rt-fMRI NFT in 120 participants with CUD.

**Methods:**

We examine a single ketamine infusion, three sessions of reward imagery rt-fMRI NFT, and the combination of those interventions contrasted to a placebo infusion or a sham NFT in 120 participants with CUD. The study is designed in a randomized, placebo-controlled, double-blind fashion with four study arms.

**Discussion:**

We expect both interventions to have a positive effect on the proportion of cocaine use days. We predict glutamate levels in the reward system to increase with the ketamine infusion and to reduce craving, a re-enhanced sensitivity towards natural rewards resulting from the rt-fMRI NFT, and synergistic effects of the combined interventions. This neurobiologically informed approach has the potential to open new avenues for the treatment of CUD through individualised and integrated pharmaco-psychotherapy.

Trial registration.

NCT06125054 ClinicalTrials.gov. Registered on October 26, 2023.

**Supplementary Information:**

The online version contains supplementary material available at 10.1186/s13063-025-08982-9.

## Administrative information

Note: the numbers in curly brackets in this protocol refer to SPIRIT checklist item numbers. The order of the items has been modified to group similar items (see http://www.equator-network.org/reporting-guidelines/spirit-2013-statement-defining-standard-protocol-items-for-clinical-trials/)

## Introduction

### Background and rationale {6a}

Cocaine is the most frequently used stimulant worldwide and its use is associated with great harm to the individual in question and their surroundings [1, 2]. Europe experienced a continuous upward trend in consumption rates over the past decade [3, 4]. In 2018, around 72,000 people in Europe sought specialised treatment for cocaine use disorder (CUD) [1]. Until today, there is no approved pharmacotherapy for CUD and psychotherapeutic interventions only show moderate effect sizes [5, 6]. This is due to (i) a limited understanding of its neurobiological underpinnings, and (ii) the fact that current psychotherapies do not specifically address the maladaptive learning processes that are associated with CUD [7, 8].

#### Diminished reward sensibility in substance use disorders

Generally, one characteristic of substance use disorders (SUD) is a remodelled reward system which is reflected in modifications within the cortico-striatal network [9–11]. This alteration in the reward system is believed to underlie maladaptive reward-seeking behaviour [12]. While exposed to substance-related stimuli, the responsiveness of the prefrontal cortex (PFC) [9–11] and nucleus accumbens (NAcc) [9, 10] is heightened, which in turn is linked to increased craving [9, 13]. On the other hand, the sensitivity of the PFC and NAcc for naturally rewarding cues (e.g. food, sex, social interaction) is reduced [14, 15]. Therefore, this shift in sensitivity to cocaine-related as compared to natural rewards [16–18] might explain why individuals with CUD choose to take substances over other rewarding activities.

#### The role of glutamate in substance use disorders

Maladaptive reward-seeking behaviour has been linked to impairments in the glutamate homeostasis in the NAcc by both human [19] and animal [20, 21] studies, pointing to a key role of glutamate signalling in SUD. In animal models of CUD, rodents show an overflow of glutamate in the NAcc when being presented with cocaine cues or cocaine probes during a withdrawal state [19, 20] that is linked with subsequent drug-seeking and self-administration. Thus, targeting the glutamatergic system is a promising pharmacological treatment approach to dampen craving and reduce cocaine use. However, no effective compound for CUD treatment has been identified for humans yet, despite extensive efforts to test glutamate affecting interventions in clinical trials [21, 22].

#### Ketamine’s effect on glutamate signalling

Ketamine, an established anaesthetic and known N-methyl D-aspartate (NMDA) receptor antagonist, affects the glutamatergic transmission in the brain [23]. In a preliminary study with rodents, investigators found a significant increase in glutamate in the NAcc after a ketamine injection [24]. Besides its anaesthetic properties, ketamine has antidepressant qualities [25] and shows preliminary promising results in the treatment of SUDs [26–29]: in both alcohol use disorder and CUD, less craving was observed and the number of days of abstinence was greater for individuals in the ketamine group compared to the control group. To gain a better understanding of ketamine’s mechanism of action, proton magnetic resonance spectroscopy (^1^H-MRS) provides in vivo and non-invasive insight into neurometabolism [30]. With a tailored approach, it is possible to measure glutamate levels even in small subcortical regions such as the NAcc [31]. Therefore, we will investigate if ketamine changes glutamate levels in patients with CUD in the NAcc together with its impact on the cue-induced increase of glutamatergic transmission associated with craving states. In addition, we will test if baseline levels of glutamate in the NAcc might serve as a potential biomarker predicting the clinical outcomes of the study and therefore are capable of assisting a stratified treatment approach in SUD. Furthermore, in addition to its direct effects on glutamatergic neurotransmission, ketamine is thought to increase synaptic neuroplasticity by promoting long-term potentiation (LTP) and inhibiting long-term depression (LTD) in neurons [32, 33], key substrates of learning- and memory-related synaptic plasticity typically involving the activation of NMDA and alpha-amino-3-hydroxy-5-methyl-4-isoxazolepropionic acid (AMPA) receptors. Via AMPA activation and a subsequent augmented release of brain-derived neurotrophic factor (BDNF) [34–37] and mTOR [35, 38], ketamine promotes protein synthesis, synaptogenesis, and strengthening of existing synapses [37–40]—all prerequisites of neuroplasticity. This supports the notion that ketamine opens a window of opportunity for learning and plasticity.

#### Modulation of reward learning by means of neurofeedback

Neurofeedback training (NFT) based on real-time fMRI (rt-fMRI) assists people to acquire and optimise individualised cognitive strategies to control activity within a specific brain region based on “real-time” feedback about the brain’s activity as assessed by fMRI [41]. This method has been successfully applied not only in healthy participants but also in individuals with SUD [42]. Furthermore, reward imagery rt-fMRI NFT was successfully applied by individuals with CUD for self-regulating small midbrain structures within the reward circuitry like the ventral tegmental area (VTA) [43] and the NAcc [41, 44]. In a previous pilot study, we could show that regular cocaine users can learn to self-regulate activity within the midbrain region with the assistance of rt-fMRI NFT, comparable to healthy participants. Interestingly, the ability to activate VTA by means of non-drug-related rewarding imagery was negatively correlated with cocaine craving and lifetime use of cocaine [43]. Therefore, the results suggest a potential therapeutic benefit of this approach for treating CUD by helping to reestablish sensitivity to non-drug-related rewards and to potentially reduce drug-taking behaviour. A reduced self-regulation in those with more severe CUD and a lack of transfer effects after a single training session highlights the need for repeated sessions and therefore more training and an optimised NFT paradigm. With those changes in the NFT setup, we believe rt-fMRI NFT of reward-related brain regions that enhances the sensitivity of non-substance-related rewards constitutes a novel and promising therapeutic approach for CUD.

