#### Primary outcomes

This study primarily seeks to determine whether the interventions, namely the single ketamine infusion, the reward imagery rt-fMRI NFT, and those two interventions combined compared to the placebo conditions show a therapeutic effect by reducing the proportion of cocaine use days. The primary efficacy value is the proportion of cocaine use days between intervention groups on follow-up visit (t3). This is measured using the timeline follow back for cocaine use, which is a standardised and validated instrument to assess cocaine use [57].

In addition to the treatment outcome, the mechanism of action of the interventions is assessed. Firstly, changes in accumbal glutamate levels in the NAcc on the intervention visit I (t1) before and during the ketamine/placebo infusion and on the following intervention visit II (t2), approximately one week after the ketamine/placebo administration are measured by using ^1^H-MRS. Secondly, the mechanistic effects of the reward imagery rt-fMRI NFT are assessed by measuring its clinically relevant transfer effect, which is defined as the difference in performance on the intervention visit I (t1) and the intervention visit II (t2) measured in the percent signal change in the NFT region by using rt-fMRI.

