
#### Other outcomes of interest

An electrocardiogram (ECG) and a clinical interview will be conducted and evaluated at the screening visit (t0) to ensure mental and physical health. To capture the consumption pattern of cocaine and potentially other psychoactive substances, the Interview for Psychotropic Drug Consumption [72] will be conducted on screening visit (t0), intervention visit I (t1), intervention visit II (t2), follow-up visit (t3), and virtual visit (t4).

On intervention visits I (t1) and II (t2) and the follow-up visit (t3), we are conducting qualitative interviews to assess acute and sustained effects of the interventions on the subjective experience and the predictive value of those effects [73, 74].

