## Assignment of interventions: allocation

### Sequence generation {16a}

Each participant gets a subject code, which is generated by the investigator at study inclusion and is individually allocated. The randomisation of the four study arms is counter-balanced with a 1:1:1:1 allocation ratio as per a computer-generated randomisation schedule using the method of minimisation, with age, gender, and severity of CUD based on the assessment of the DSM-5 criteria by the structural interview MINI [75] at the screening visit (t0) (mild and moderate vs. severe) as binary minimisation variables.

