## Statistical methods

### Statistical methods for primary and secondary outcomes {20a}

The central hypothesis that the active treatments reduce the “proportion of cocaine use days” is tested by implementing an analysis of covariance (ANCOVA) with the between-subjects factor treatment groups (i.e. rt-fMRI NFT/placebo, rt-fMRI NFT/ketamine, sham NFT/placebo, and sham NFT/ketamine) once for each treatment (i.e. NFT and ketamine) for the follow-up visit (t3). The initial ANCOVA includes variables that potentially differ between groups at baseline as potential confounding variables, namely age, gender, substance use, and severity of dependence. To retain the simplest model, all the baseline variables that do not contribute to the outcome variable ‘proportion of cocaine use days’ are excluded from the model. Should none of the baseline variables that differ between groups contribute to the outcome variable, an analysis of variance (ANOVA) is performed. Post-hoc tests are adequately corrected for multiple comparisons.

Changes in glutamate levels in the NAcc due to the ketamine infusion on intervention visit I (t1) are analysed by applying an ANOVA for repeated measurements as not many dropouts for one of the pre-ketamine and post-ketamine glutamate assessments are expected. The main source of dropouts is expected to be of technical nature, causing insufficient data quality of the ^1^H-MRS, while dropout due to lack of compliance between the two measurements is less plausible since they take place on the same day. The ANOVA for repeated measurements includes the between-group factor treatment group (i.e. rt-fMRI NFT/placebo, rt-fMRI NFT/ketamine, sham NFT/placebo, and sham NFT/ketamine) and the within-group factor time (pre-ketamine infusion vs. post-ketamine infusion). Post-hoc test is adequately corrected for multiple comparisons. To test for sustained effects of the ketamine infusion on glutamate concentrations in the NAcc between intervention visit I (t1) and intervention visit II (t2), a multilevel analysis is applied that allows to (i) analyse multiple events in one model, (ii) include subjects with incomplete data sets, (iii) account for different time intervals between the events (7 to 14 days).

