The transfer effect of the reward imagery rt-fMRI NFT from the first to the second session is analysed by comparing the percent signal change in the practice run from the first reward imagery rt-fMRI NFT session (t1) and the transfer run from the third reward imagery rt-fMRI NFT session (t2) in an ANOVA for repeated measurements with a between-subject factor treatment group (i.e. rt-fMRI NFT/placebo, rt-fMRI NFT/ketamine, sham NFT/placebo, and sham NFT/ketamine) and the within-group factor time (first session at t1 vs. third session at t2). Post-hoc tests are adequately corrected for multiple comparisons. To test the impact of fatigue or of earlier reward imagery rt-fMRI NFT success on the transfer effect, an exploratory analysis with a multilevel analysis is performed that enables to include multiple events, in this case the transfer run from the first reward imagery rt-fMRI NFT session and the practice run from the third reward imagery rt-fMRI session, thereby accounting for different time intervals between those four events.

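### The neurofeedback transfer model leaves out CUD severity (a minimisation factor) and t0 craving, which may cost a little precision at no saving

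*Protocol article*

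**What the plan says.** **Pilot findings.** In the Introduction, under the heading on neurofeedback and reward learning, the group's pilot is reported. The ability to activate the VTA through non-drug reward imagery "was negatively correlated with cocaine craving and lifetime use of cocaine". The same paragraph names "A reduced self-regulation in those with more severe CUD and a lack of transfer effects after a single training session" as reasons for repeated sessions. No coefficients are given.

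**Outcome.** Under Primary outcomes, the clinically relevant transfer effect is "defined as the difference in performance on the intervention visit I (t1) and the intervention visit II (t2"), measured as percent signal change in the neurofeedback region.

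**Model.** Statistical methods {20a} compares the practice run of the first session (t1) with the transfer run of the third session (t2) "in an ANOVA for repeated measurements with a between-subject factor treatment group" (four arms) and the within-person factor time. No covariate is named. The only covariate list in that section, "namely age, gender, substance use, and severity of dependence", belongs to the ANCOVA of cocaine use days and is subject to data-driven removal.

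**Available data.** Severity is rated by the MINI at t0 and used in Sequence generation {16a}, where it is dichotomised: "mild and moderate vs. severe) as binary minimisation variables". OCCUS is scheduled at t0 in Table 1. A drug consumption interview is also held at t0, under Other outcomes of interest: "To capture the consumption pattern of cocaine and potentially other psychoactive substances". The article does not say that it yields lifetime use.

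**The concern.** The protocol links craving and severity to VTA self-regulation, uses severity to allocate participants, and then sets out a model for the self-regulation outcome that contains neither. There are two possible consequences:

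- **Precision.** If a t0 variable explains part of the between-person variation in the t1-to-t2 change, that part stays in the error term and the interval for real against sham neurofeedback is wider than it need be.
- **Calibration.** Minimisation forces the arms to be alike on severity. If severity predicts the change, the arm difference varies less than the unadjusted error term implies, so the test rejects too rarely under the null.

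Neither consequence biases the comparison. What is at stake is some power for a mechanistic outcome.

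**Working it through.** **1. The plan's own figures.** Sample size {14} gives 21 per group (84 in total) and 111 in total, both for ¹H-MRS at d = 0.80. No figure is given for the transfer outcome, so there is none to reproduce.

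**2. What the planned test compares.** With two time points, the group-by-time test is an ANOVA on the change score. Take equal unit variances, ρ for the correlation between the two runs, and r₁ and r₂ for the correlations of a t0 covariate with the t1 practice run and the t2 transfer run. Then

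- Var(change) = 2(1 − ρ)
- Cov(covariate, change) = r₂ − r₁
- R² of change = (r₂ − r₁)² / [2(1 − ρ)]

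The standard error after adjustment is multiplied by √(1 − R²). The protocol gives none of r₁, r₂ or ρ, so every value below is an assumption. With ρ = 0.5 the denominator is 1.

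| r₁ | r₂ | R² of change |
|---|---|---|
| 0.4 | 0.4 | 0 |
| 0.3 | 0.5 | 0.2² = 0.04 |
| 0 | 0.3 | 0.3² = 0.09 |
| 0 | 0.5 | 0.5² = 0.25 |

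The first row is a covariate tied to a stable level. Differencing has already removed it. A simulation with correlations of −0.4 at both runs (30 per arm) gave a standard error of 0.180 unadjusted and 0.181 adjusted.

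**3. Power.** Assume real against sham, 60 v 60 (four arms of 30, pooled over the infusion), standardised change difference d = 0.5, two-sided 5%, two-sample t test with 118 degrees of freedom. The noncentrality is 0.5 × √(60/2) / √(1 − R²) = 2.739 / √(1 − R²).

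| R² | √(1 − R²) | Noncentrality | Power | Equivalent extra participants, 1/(1 − R²) − 1 |
|---|---|---|---|---|
| 0 | 1 | 2.739 | 77.5% | 0% |
| 0.04 | 0.980 | 2.795 | 79.2% | 4% |
| 0.09 | 0.954 | 2.871 | 81.3% | 10% |
| 0.25 | 0.866 | 3.162 | 88.0% | 33% |

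**4. Effect of minimising on severity and then ignoring it.** Simulation of 120 people in four arms, minimised on three binary factors with an assumed 80% probability of the best arm (the protocol states none), 4,000 runs, outcome the t1-to-t2 change, d = 0 or 0.5. R² is the share of change variance due to severity.

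| R² | Type I error, unadjusted v adjusted | Power, unadjusted v adjusted |
|---|---|---|
| 0 | 5.0% v 4.9% | 78% v 78% |
| 0.04 | 4.5% v 4.7% | 77% v 78% |
| 0.09 | 3.4% v 4.3% | 79% v 82% |
| 0.25 | 2.7% v 5.1% | 81% v 88% |

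The Monte Carlo standard error of a 5% rate is √(0.05 × 0.95 / 4000) = 0.34 percentage points, so differences of a few tenths mean nothing. The pattern is that adjustment costs nothing at R² = 0, and the unadjusted test becomes more conservative as R² grows.

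**5. Degrees of freedom.** The four-arm change model has 120 − 4 = 116 residual degrees of freedom. Two covariates leave 114 and three leave 113.

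**The case against.** The strongest reply is that the pilot finding concerns the level of VTA activation, whereas the outcome is a within-person change. For a predictor of level alone the gain is exactly zero. **This stands.** A reader might infer from the Introduction that precision is certainly being lost, or that craving, lifetime use and severity are established predictors of transfer. The protocol supports neither: it reports correlations without coefficients, does not relate them to change between sessions, and does not show that they hold for a signal from the sham region.

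Some of the answer to this also stands. The t1 run precedes all feedback and the t2 run follows three sessions, and the authors themselves took weaker self-regulation in severe CUD as a reason for more training. It is therefore plausible, though not shown, that these variables relate more to the trained result than to the untrained start.

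Three further objections:

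- **Severity may not be a separate finding.** The sentence on more severe CUD names no scale and may only summarise the correlations with craving and lifetime use. Nor does the article say that the pilot measured craving by OCCUS. Both are fair. Severity nevertheless has an independent claim, because it is an allocation factor.
- **The allocation argument reaches age and gender too.** True. The point is confined to severity because the protocol relates only that minimisation factor to self-regulation.
- **Covariates belong in the analysis plan, which is not shown.** That would answer a complaint about missing detail. Here the article states the model, and the point concerns that statement. An unadjusted group-by-time test in a randomised trial remains valid, so this is an improvement and not an error.

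The correlations with severity planned under Methods for additional analyses {20b} examine whether effects depend on it. They do not adjust the transfer model.

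**Conclusion.** The point holds as a minor, inexpensive improvement. The stated transfer model omits an allocation factor and a t0 measure of craving, both of which the protocol associates with self-regulation.

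The size of the benefit cannot be derived from the protocol. On the assumptions d = 0.5, 60 v 60 and two-sided 5%, an R² of change from 0 to 0.09 takes power from about 78% to 81–82%. Ignoring severity at R² = 0.09 lowers the type I error to roughly 3.4%. The R² = 0.25 row (88% power) should not be read as an expected gain: at ρ = 0.5 it needs a covariate unrelated to the first run and correlated 0.5 with the last. Zero gain is a real possibility.

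Lifetime cocaine use is not confirmed as a t0 variable, so its absence from the model cannot be counted as a lost opportunity.

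**What to change.** In Statistical methods {20a}, add to the transfer analysis, as fixed covariates, CUD severity in the two categories used for allocation and the t0 OCCUS craving score. Each should enter with its interaction with time, because a main effect alone does not reach the change contrast. In the equivalent change-score form they enter simply as covariates. State that they stay in the model whatever their significance, so that the removal rule of the cocaine-use ANCOVA does not carry over. Add lifetime cocaine use, in the same way, only if the t0 interview records it.

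The cost is a wording change, no new data and two or three of 116 residual degrees of freedom. The benefit may be nil.
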